### Procedures

The study will begin with a screening process using a consecutive sampling approach to ensure that all eligible individuals are considered for participation. Patients will be evaluated based on the inclusion and exclusion criteria, and those who meet the eligibility requirements will be invited to participate. Prior to enrollment, patients will receive comprehensive information about the study’s purpose, procedures, potential risks, and benefits. After having the opportunity to ask questions, those willing to participate will provide written informed consent before proceeding further.

To maintain methodological rigor, randomization will be conducted using a block randomization method with allocation concealment via sealed opaque envelopes, ensuring an unbiased assignment of participants to either study arm.

All participants must sign a written informed consent form before engaging in the study. They will be assured that their participation is voluntary and that they have the right to withdraw at any time without any consequences for their standard medical care. Further details regarding follow-up assessments are described in the section on Follow-ups.

### Enhanced educational intervention (Group A)

Patients assigned to Group A will receive an enhanced educational intervention designed to improve their understanding and acceptance of IC. This intervention consists of standard clinical practice training supplemented with an informational booklet and a video tutorial. The educational materials will provide detailed instructions on the proper use and benefits of IC. The primary goal of this enhanced intervention is to empower patients by providing them with knowledge and skills that enable them to perform intermittent catheterization effectively and confidently, ultimately improving adherence and acceptance rates.

### Standard clinical practice training (Group B)

Patients in Group B will receive standard clinical practice training, which consists of basic instructions and demonstrations provided by healthcare professionals on how to perform intermittent catheterization correctly. This training will focus primarily on the technical aspects of catheterization, including proper aseptic techniques, insertion and removal procedures, and hygiene practices to prevent infections. However, this training will not include the additional educational materials provided to Group A, such as the informational booklet and video tutorial on the no-touch sheath and protective tip catheters. While the standard training ensures that patients receive essential knowledge on catheterization, it does not provide reinforced learning tools designed to enhance acceptance and adherence, as in the enhanced intervention.

### Follow-ups

Data collection will occur at three key time points throughout the study. The initial training session (T0) will serve as the baseline assessment. The first follow-up (T1) will be conducted one month after the initial training to assess early outcomes, while the second follow-up (T2) will take place three months after the initial training to evaluate short-term effects. These follow-up assessments will allow for the monitoring of changes in acceptance, adherence, and patient-reported outcomes over time.

### Measurements

Sociodemographic and clinical data will be collected to comprehensively understand the patient population and the factors influencing adherence and acceptance of IC.

Sociodemographic data will include age, gender, educational level, employment status, marital status, and socioeconomic status. Age will be recorded to analyze the distribution of the patient population and its potential impact on IC adherence. Although the study focuses on male patients, gender-related data may still be relevant for broader analyses [13]. The educational level will be documented as it may influence the patient’s understanding of medical instructions and adherence to IC routines. Employment status will be considered, as work-related stress and availability could impact adherence, while marital status will be evaluated to assess the role of social support in adherence and overall well-being. Socioeconomic status will also be examined, as economic factors may influence access to healthcare resources and compliance with prescribed treatments.

Clinical data will include primary diagnosis, condition duration, previous treatments, comorbidities, medication use, urinary function, and prior IC experience. The type of Neurological disease in patients having neurogenic bladder will be recorded, identifying whether it results from conditions such as spinal cord injury, multiple sclerosis or others. The duration of the condition will be noted, as the length of time since diagnosis may impact the patient’s adaptation to IC. A detailed history of previous treatments will be collected, including surgeries, medications, and prior catheterization experiences. Comorbidities such as diabetes or cardiovascular diseases will be assessed to determine their potential impact on overall health and IC adherence. Medication use, particularly drugs related to urinary symptoms, will be recorded to understand their effect on catheterization efficacy and adherence. Baseline urinary function will be evaluated to correlate with changes observed throughout the study. Additionally, previous IC experience, if any, will be documented to provide context for current acceptance and adherence levels.

Self-report assessments will be administered to evaluate different aspects of the patient’s experience, adherence, and outcomes related to IC. All measurement tools selected for this study are supported by evidence of validity and reliability:(a)The Intermittent Catheterization Acceptance Test (I-CAT) will be administered at baseline (T0), one month post-initial training (T1), and three months post-initial training (T2). The I-CAT is designed to measure changes in acceptance rates of IC over time. It evaluates psychological comfort, willingness, and overall acceptance, helping to assess how well patients adapt to the procedure and the impact of educational interventions on their acceptance levels [10].(b)The Urinary Symptoms Questionnaire for Neurogenic Bladder in IC (USQNB-IC) will be conducted at T0, T1, and T2. This instrument evaluates urinary symptoms in patients with neurogenic bladder undergoing IC. It measures the severity and frequency of symptoms, including incontinence, urgency, and discomfort, allowing for the monitoring of symptomatic changes and potential improvements in urinary health with consistent IC use [14].(c)The Intermittent Catheter Adherence Scale (I-CAS) will be administered at T1 and T2 to measure adherence to the prescribed IC regimen. This tool assesses the frequency and consistency of catheter use as recommended by healthcare providers. Evaluating adherence through I-CAS will help identify barriers to consistent IC and assess the effectiveness of educational interventions in improving compliance [11].(d)The Autonomy Checklist will be completed at T0, T1, and T2 to assess procedural autonomy in IC. This checklist evaluates the patient’s ability to independently manage catheterization, including preparation, insertion, and hygiene maintenance. High scores indicate successful training and an increase in self-sufficiency in performing IC.(e)The Serendipity Questionnaire, developed by the researchers involved in this research, will be administered at T2 to capture subjective experiences and unexpected positive outcomes during the IC journey. This questionnaire includes items that explore patient insights, satisfaction, and any unexpected benefits they may have encountered. The qualitative data obtained will provide a richer understanding of the patient experience beyond clinical measures.(f)The Quebec User Evaluation of Satisfaction with Assistive Technology (QUEST) will be administered at T1 and T2 to assess patient satisfaction with the assistive devices used for IC. This instrument includes questions about the ease of use, effectiveness, and overall satisfaction with the catheter and related equipment. By identifying areas for improvement in device design and patient training, QUEST ensures that tools meet the practical needs of patients [15].(g)Motor function assessments will also be included in the study. The Motor Assessment using a Dynamometer will be conducted at T0 and T1 to measure grip strength, an essential factor in the ability to perform IC independently [16]. This test will help determine whether physical limitations may impact a patient’s ability to handle and use the catheter effectively by evaluating motor strength. The Manual Dexterity Assessment using the Nine Hole Test will be performed at T0 and T1 to measure fine motor skills, which are crucial for successful IC execution [17]. This test requires participants to place and remove pegs from a board, providing a quantitative measure of hand function. It will help identify patients who may require additional support or adaptive techniques to manage IC effectively.

### Statistical plan

The statistical analysis of this study will begin with descriptive statistics to summarize the baseline characteristics of participants, including sociodemographic and clinical data, under intention-to-treat analysis. Continuous variables will be presented using means, medians, standard deviations, and interquartile ranges, depending on their distribution. Categorical variables will be summarized using frequencies and percentages.

Inferential statistical analyses will be conducted to compare outcomes between the enhanced educational intervention group and the standard clinical practice training group. Independent *t*-tests will be used to compare normally distributed continuous variables, while Mann-Whitney U tests will be applied for skewed distributions and for the primary outcome (I-CAT score at T2). Chi-square tests will be used to compare categorical variables between the study groups.

Correlation analyses will be conducted following these comparisons to explore relationships between key study variables. Specifically, associations between IC acceptance scores (I-CAT), adherence levels (I-CAS), urinary symptoms (USQNB-IC), and functional abilities (Autonomy Checklist and motor assessments) will be examined. Depending on the distribution of the data, either Pearson’s correlation coefficient (for normally distributed variables) or Spearman’s rank correlation coefficient (for non-normally distributed variables) will be used. These analyses will help identify how different aspects of the patient experience and clinical characteristics interrelate, providing insight into the factors influencing IC acceptance and adherence.

To further investigate factors associated with adherence and secondary outcomes, multivariable analyses will be performed. Logistic regression models will be used to analyze binary outcomes, such as adherence status, while linear regression models will be applied to continuous outcomes, including I-CAT scores. Predictor variables will include sociodemographic factors (e.g., age, education level, socioeconomic status), clinical characteristics (e.g., primary diagnosis, comorbidities), and intervention type (enhanced educational intervention vs. standard clinical training). Interaction terms will be incorporated to assess whether the effects of the intervention differ across subgroups, ensuring a comprehensive evaluation of potential effect modifiers. Model selection will be guided by theoretical considerations and statistical criteria, using stepwise or backward elimination methods to refine the models.

Handling missing data will be an important aspect of the analysis. This study assumes that data are missing at random (MAR), meaning that missingness is related to observed data but not to unobserved data [18]. All instances of missing data will be identified and documented, and patterns of missingness will be analyzed to determine whether they are systematically related to specific variables. Descriptive statistics will be used to summarize the extent and distribution of missing data for each variable.

Multiple imputation will be used as the primary method for handling missing data to minimize bias and preserve statistical power [19]. This approach generates multiple plausible datasets by imputing missing values based on observed data, which are then analyzed separately. The results from these datasets will be combined to produce estimates and confidence intervals that appropriately reflect the uncertainty introduced by missing data. Multiple imputations using chained equations will be performed, suitable for handling various variables, including continuous, binary, and categorical data.

To evaluate the robustness of the findings, sensitivity analyses will be conducted, comparing the results of multiple imputations with alternative approaches, such as complete case analysis (where only participants with complete data are analyzed) and single imputation methods [18]. These analyses will ensure that the handling of missing data does not introduce bias into the study conclusions. The extent of missing data, the imputation methods applied, and the results of sensitivity analyses will be transparently reported in all study publications and presentations to ensure scientific integrity and reproducibility.

All statistical analyses will be performed using R (R Core Team, 2023). The significance level (alpha) for hypothesis testing will be set at 5 % (0.05). When multiple comparisons are conducted, appropriate adjustment procedures will be applied to control for Type I error inflation. Two-tailed tests will be employed for all analyses.

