### Randomization and allocation concealment

A randomization list of 20 cases per center, allocated in a 1:1 ratio between the intervention (Group A) and control (Group B) arms, will be created using a simple randomization algorithm. Simple randomization was deemed appropriate for this study, given the limited number of patients, ranging from 4 to 20, expected to be enrolled at each center. Unlike block randomization, which could create challenges if a center fails to complete an entire block, simple randomization ensures flexibility while maintaining methodological rigor.

The randomization list will be generated independently by the methodologist responsible for the process, ensuring no bias or influence from investigators. This list will be securely stored and concealed from the principal investigator (PI) and study centers to maintain strict allocation concealment.

The randomization process will employ a sealed, opaque envelope system to ensure allocation concealment. For each center, 20 envelopes will be prepared, corresponding to the 20 cases on the randomization list. Each envelope will be sequentially numbered from 1 to 20 and will contain the group assignment (Group A or Group B) based on the randomization list. The envelopes will be opaque and sealed to prevent any possibility of visual identification of group assignments before opening.

Once prepared, the envelopes will be sent to each participating center in a tamper-proof package by the methodologist who created the randomization list. The randomization list will remain securely stored, ensuring that neither the PI nor the study sites have access to it. At each center, envelopes will be opened sequentially and in numerical order by a designated study coordinator after confirming the patient’s eligibility and obtaining written informed consent. The study coordinator will be trained to ensure compliance with the protocol and will have no involvement in delivering the intervention or assessing outcomes, maintaining a clear separation of roles and minimizing bias.

All randomization and allocation processes will be systematically documented. Once an envelope is opened, the group assignment will be recorded, and the envelope will be securely stored to maintain an audit trail. The randomization and envelope-opening processes will be periodically audited to ensure adherence to the protocol and to detect any deviations that may compromise allocation concealment.

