### Sample size

The sample size for this study was determined to ensure sufficient statistical power to detect a meaningful difference in median I-CAT scores between the intervention and control groups. The primary endpoint aims to demonstrate an improvement in median I-CAT scores from 3.0 to 3.5, which corresponds to an increase from the median acceptance score to the 75th percentile of the previously reported distribution [10,11].

To achieve this, a significance level of 0.05 (5 %) was selected, meaning there is a 5 % probability of a Type I error, where a difference is incorrectly concluded when none exists. A power of 80 % (0.80) was chosen, ensuring that the study has an 80 % probability of detecting a true difference between the groups if one exists, thereby reducing the risk of a Type II error. Based on previous studies and pilot data, a standard deviation of 1 was assumed for the calculation [10,11]. Given these parameters, the sample size calculation was performed using a non-parametric (Mann-Whitney U) test to compare the two independent groups.

The formula used for calculating the required sample size accounts for effect size, significance level, and power. The required sample size per group, denoted as n, is calculated using the equation:(1)$$n=\frac{{\left(Z_{\alpha /2}+Z_{\beta }\right)}^{2}\times \;2\;\times \sigma^{2}}{\Delta^{2}}$$

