## Limitations

Several limitations should be acknowledged regarding this protocol, which resulted in the tradeoff between feasibility and optimal solutions to mitigate the risk of biases. One potential limitation is the reliance on self-reported measures, such as the I-CAT and the I-CAS. Self-reported data may be subject to social desirability bias or recall bias, potentially affecting the accuracy of adherence and acceptance measurements. While validated tools are used to mitigate these issues, objective adherence measures, such as tracking actual catheter use, are not included in the protocol. Another limitation is the follow-up period of three months (T2), which may not fully capture long-term adherence and sustained acceptance of intermittent catheterization (IC). Although three months provides insight into short- and medium-term outcomes, future studies with extended follow-up periods may be needed to assess long-term patient adherence and potential changes in acceptance beyond the study period. The study also focuses exclusively on male patients, which limits the generalizability of findings to female populations. While this design choice was made to reduce variability in anatomical and procedural differences, future research should evaluate whether the educational intervention is equally effective in female patients requiring IC.

Additionally, the multicenter design introduces variability in clinical practice settings, patient populations, and training approaches, which may impact intervention fidelity. Although efforts will be made to standardize training and ensure protocol adherence across study sites, minor differences in educational delivery and patient interactions could influence outcomes. Finally, while the sample size calculation is based on a clinically meaningful effect size (0.5-point increase in I-CAT scores at T2), the study may be underpowered to detect more minor but still relevant improvements. Sensitivity analyses have considered a range of effect sizes, but if the actual effect is smaller than anticipated, the study may lack sufficient power to demonstrate statistical significance. Although the sample size is adequately powered to detect the primary outcome, caution should be exercised in generalizing the results to broader populations, especially given the inclusion of only male patients and the potential variability across clinical centers.

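### The primary test compares I-CAT at T2 without using the T0 I-CAT already collected, which gives up precision (not validity) by an amount that depends on an unstated correlation

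*Protocol article*

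**What the plan says.** The Statistical plan names the primary test: "Mann-Whitney U tests will be applied for skewed distributions and for the primary outcome (I-CAT score at T2"). It attaches no covariate or stratum to that test. It also states "The significance level (alpha) for hypothesis testing will be set at 5 % (0.05") and "Two-tailed tests will be employed for all analyses".

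The baseline value is available. Under Measurements, "The Intermittent Catheterization Acceptance Test (I-CAT) will be administered at baseline (T0"), and again at T1 and T2.

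The outcome is worded in more than one way. Study design calls it the change in I-CAT. Primary endpoint calls it improvement in the median at T2. The Specifications table and the Statistical plan use the score at T2.

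Regression models for I-CAT scores do appear later in the Statistical plan, but as a further investigation of associated factors and secondary outcomes, with terms chosen by stepwise or backward elimination. There, "Predictor variables will include sociodemographic factors (e.g., age, education level, socioeconomic status), clinical characteristics (e.g., primary diagnosis, comorbidities), and intervention type". Neither baseline I-CAT nor centre is named.

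On centres, the randomisation section provides "A randomization list of 20 cases per center", produced by simple randomisation, with 4 to 20 patients expected at each of 17 sites. Limitations accepts that "the multicenter design introduces variability in clinical practice settings, patient populations, and training approaches".

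**The concern.** The T0 I-CAT is the same instrument in the same patient, so it is the natural candidate for predicting the T2 score. If the two are correlated, a T2 comparison that ignores T0 leaves explainable variation in the error and needs more patients for the same power. The protocol has little room to spare: it says "A power of 80 % (0.80) was chosen", describes no allowance for dropout in its Sample size section, and concedes under Limitations that it may be underpowered for smaller effects.

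There is also a mismatch of wording. An outcome described as change is tested by a method that never uses the starting value. A T2 comparison adjusted for T0 would serve both descriptions.

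**Working it through.** **Inputs from the protocol.** Difference 0.5 (3.0 to 3.5), SD 1, two-sided alpha 0.05, power 80%, 1:1 allocation, 64 per group, 17 centres. **Assumed, because not given:** the T0–T2 correlation r, the shape of the score distribution, and the intraclass correlation (ICC) for centre.

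**1. The protocol's own figure.** Its equation gives n = 2 × (1.96 + 0.84)² × 1² / 0.5² = 62.7, so 63 per group. The t-test version gives 63.8, so 64. The stated 64 is reproduced.

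**2. The planned test at that size.** Under normality the Mann-Whitney test has efficiency 3/π relative to the t-test. The effective size is 64 × 3/π = 61.1 per group and power is 78.3%. This does not depend on r, because the test does not use T0.

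**3. What T0 is worth in a linear model.** Adjustment multiplies the residual variance by 1 − r².

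| r (assumed) | 1 − r² | n per group for 80% power | power at 64 per group |
|---|---|---|---|
| 0 | 1.00 | 63 | 81% |
| 0.3 | 0.91 | 58 | 84% |
| 0.5 | 0.75 | 48 | 90% |
| 0.6 | 0.64 | 41 | 94% |

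These use the normal approximation. The r = 0 row already exceeds 78% only because a parametric test is being compared with a rank test on normal data. The comparison that isolates baseline is rank against rank.

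**4. Rank against rank.** Simulated power, normal scores, 64 per group, difference 0.5:

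| r (assumed) | Mann-Whitney, unadjusted | rank ANCOVA on arm and T0 |
|---|---|---|
| 0 | 78–79% | about 78% |
| 0.3 | 78–79% | about 81% |
| 0.5 | 78–79% | about 88% |
| 0.6 | 78–79% | about 91% |

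**5. Shape.** The protocol puts the 75th percentile 0.5 above the median with SD 1. A normal distribution with SD 1 would put it 0.67 above. A Laplace distribution with SD 1 would put it at ln 2 / √2 = 0.49. With Laplace scores, linear ANCOVA at r = 0.3 has 82% power against 90% for the planned Mann-Whitney. At r = 0.5 the rank-based adjusted analysis has 97% against 92%. So the advantage of adjusting survives heavy tails if the method stays rank-based or ordinal, but not reliably if it is linear.

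**6. Validity.** Simulated under the null with simple randomisation, r = 0.5 and centre ICC 0.05 or 0.10, the unadjusted Mann-Whitney rejects in 5.2% of runs.

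**7. Change score.** With SD 1 at each visit, an unadjusted change has variance 2(1 − r). At r = 0.3, n = 62.7 × 1.4 = 87.8, so 88 per group. At r = 0.5, n = 62.7 × 1.0, so 63. Testing the change itself therefore does not replace adjustment.

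**8. Centre.** With 128/17 = 7.5 patients per centre on average and simple randomisation, a random intercept with known ICC reduces the variance of the treatment effect by 1.2% at ICC 0.05 and 4.0% at ICC 0.10. That is worth about 128 × 0.012 = 1.5 to 128 × 0.040 = 5.1 patients. Adding 17 fixed centre effects to a baseline-adjusted linear model changed simulated power by between −3 and +1 points at those ICCs.

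**The case against.** The strongest reply is that nothing here is wrong. The planned test is prespecified, holds its level, and matches the test named in the Sample size section, where no adjustment was assumed. Its 78% against a nominal 80% is a trivial gap. All of that stands, and it limits the point to efficiency.

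Second, r is unknown and may be small. Participants have no or less than one month's experience of the technique, and T0 is the initial training session, so acceptance at T0 may say little about acceptance three months later. This also stands: at r near 0 there is nothing to gain, although in the simulation there is nothing to lose either.

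Third, the linear model usually proposed can do worse than the planned test if the scores are heavy-tailed, as the protocol's own percentiles hint. That is correct, and it is why the fix below keeps the primary analysis rank-based or ordinal.

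Fourth, the regression predictors are introduced by examples, so a condensed article does not prove that baseline I-CAT is excluded from those models. Granted. But those models are exploratory and do not alter the test fixed for the primary outcome.

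A reader might infer more than the protocol supports. Chance baseline imbalance does not bias the planned test, because its 5% level already allows for it. Separate simple lists per centre impose no balance within centre, so they create no obligation to adjust for centre. Nor does an ICC of 0.05–0.10 translate into a 5–10% gain in precision. The claim that ignoring centre makes the standard error too large would need blocking within centre. Procedures mentions block randomisation without saying that blocks are within centre, while the randomisation section argues for simple randomisation over blocks. Until those sections are reconciled, that argument is conditional.

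**Conclusion.** The point holds as a loss of precision from an avoidable choice, not as an error of validity. The primary comparison leaves out a baseline measurement that the trial collects and that one description of the primary outcome requires. With 64 per group and normal scores, a baseline-adjusted rank analysis would raise power from about 78–79% to about 81% at r = 0.3, 88% at r = 0.5 and 91% at r = 0.6, with no material change at r = 0. These sizes rest on an assumed r, SD 1 and a true difference of 0.5. Which row applies cannot be told from the protocol. The centre component is minor (about 1–4% of variance at an assumed ICC of 0.05–0.10) and would matter more only if allocation turns out to be blocked within centre.

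**What to change.** Before any unblinded analysis, name a single primary analysis of T2 I-CAT on arm and T0 I-CAT: either a proportional-odds model or a rank ANCOVA, chosen now, with no switch that depends on observed skewness. The power figures above were simulated for rank ANCOVA. Without covariates, the score test of the proportional-odds model is the Mann-Whitney test, so that option stays close to the present plan. It also gives a coefficient and standard error that can be combined across the planned multiple imputations.

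Keep the unadjusted Mann-Whitney as a supportive analysis, and add a baseline-adjusted linear model to report the mean difference with its confidence interval. Describe the primary outcome in the same terms in Study design, Primary endpoint and Statistical plan.

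Confirm that T0 I-CAT is completed before the envelope is opened. Follow-ups makes the training session the baseline, and in an open-label trial a T0 score given after allocation is known would not be a clean covariate.

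Reconcile simple and block randomisation between the randomisation section and Procedures. If blocking is within centre, include centre in the model. If not, a random intercept is optional.

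The cost is a few sentences, no new data and no change in the sample size. The downsides are a model assumption and an effect measure other than the difference in medians, on which the sample size was argued.

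### Stepwise or backward elimination is applied to secondary models that contain the intervention and its interactions, with the intervention not kept in, so adjusted effects can be dropped or exaggerated

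*Protocol article*

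**What the plan says.** The relevant text is in the protocol article, under Statistical plan.

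- Purpose: "To further investigate factors associated with adherence and secondary outcomes, multivariable analyses will be performed". Adherence status gets a logistic model, and "linear regression models will be applied to continuous outcomes, including I-CAT scores".
- Predictors: "sociodemographic factors (e.g., age, education level, socioeconomic status), clinical characteristics (e.g., primary diagnosis, comorbidities", together with "intervention type (enhanced educational intervention vs. standard clinical training".
- Interactions: "Interaction terms will be incorporated to assess whether the effects of the intervention differ across subgroups". Neither their number nor the subgroups are given.
- Selection: theory and statistical criteria are both to guide it, "using stepwise or backward elimination methods to refine the models". No term is exempted, no retention threshold is given, and no rule keeps a main effect while its interaction stays.
- Missing data: "Multiple imputation will be used as the primary method for handling missing data". The imputed datasets are analysed separately and the results are then combined.

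The same section tests the primary outcome, I-CAT at T2, by a Mann-Whitney U test. Other comparisons between arms use t, Mann-Whitney or chi-square tests. None of these involves selection. A general sentence promises suitable adjustment for multiple comparisons but names no procedure or family.

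**The concern.** In a randomised trial the arm is the question, not a candidate predictor. If it must earn its place by a p-value, a non-significant result is reported as no estimate rather than as an estimate with an interval. A significant one is reported from a sample already filtered for looking large. Standard p-values and intervals ignore that filtering. The same applies to interactions: those that survive are presented as effect modifiers, with no record of how many were screened.

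At stake are the adjusted intervention effects on adherence and on I-CAT, and any statement about which patients benefit more. These are secondary results, but they are the ones a reader would use to decide whom to offer the booklet and video.

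The text fixes the selection method itself. A statistical analysis plan would have to reverse that sentence, not merely add detail to it.

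**Working it through.** **1. The plan's own figure.** Inputs from Sample size: difference 0.5, SD 1, two-sided alpha 0.05, power 80%. The printed formula gives n = (1.96 + 0.84)² × 2 × 1² / 0.5² = 62.7, so 63 per group. The t-test version gives 63.8, so 64, with power 80.1%. The stated 64 per group (128 in total) reproduces and is not in dispute. It is used below.

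**2. The intervention term: how often it is lost, and what remains.** With 64 per arm and SD 1, the standard error of the difference is √(2/64) = 0.177. Removal at p>0.05 (t with 126 df, critical value 1.98) means that the term stays only if the estimate exceeds about 0.350 in absolute value. For a true effect δ, the chance of being kept is about 1 − Φ((0.350 − δ)/0.177). The mean estimate when kept is about δ + 0.177 × φ(a)/(1 − Φ(a)), with a = (0.350 − δ)/0.177. The lower tail is negligible.

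| True effect (SD) | a | Kept | Dropped | Mean when kept |
|---|---|---|---|---|
| 0.2 | 0.85 | 20% | 80% | 0.44 |
| 0.3 | 0.28 | 39% | 61% | 0.47 |
| 0.5 | −0.85 | 80% | 20% | 0.56 |

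Simulated backward elimination (n = 128, linear model, six standard normal covariates, removal at p<0.05) agrees. The arm was dropped in 79%, 61% and 20% of trials, and the mean retained estimates were 0.45, 0.47 and 0.57. The dropped column is essentially one minus power, so it does not measure harm done by elimination. The last column does: an unselected estimate would average 0.2, 0.3 and 0.5.

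A second simulation used five covariates and five interactions with the arm, and varied the rule. Each range runs over with and without a hierarchy rule.

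| True effect (SD) | Arm dropped, removal at 0.05 | Arm dropped, removal at 0.157 |
|---|---|---|
| 0.2 | 60–80% | 24–60% |
| 0.3 | 45–61% | 16–38% |
| 0.5 | 13–17% | 3–7% |

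The result therefore depends on a threshold and a hierarchy rule that the plan does not state.

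**3. False effect modifiers.** For k independent null interactions tested at 0.05, the chance of at least one is 1 − 0.95^k.

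- k = 5 (the number of covariates the plan names as examples): 22.6%. Simulated retention after elimination at 0.05: about 23–26%.
- k = 6: 26.5%. Simulated after elimination at 0.05: about 27–28%. A fixed full model with no selection gave about 25–26%.

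Most of the figure is therefore multiplicity. With hierarchy kept, selection adds roughly two points at a 0.05 rule. At a 0.157 rule with six candidates, 28–30% of trials ended with a false interaction at p<0.05. If mere retention is read as a finding, 1 − 0.843^5 = 57% of trials would keep at least one of five null interactions under the 0.157 rule.

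**4. Fit with multiple imputation.** Analysing each imputed dataset separately and then combining needs the same model in each. In a simulation assuming 15% missing outcomes, 20 imputations, five covariates and a true effect of 0.5 SD, the imputations did not all select the same model in 97% of trials. The arm was in some models but not others in 41%. The plan does not say how such results would be combined.

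**Assumptions not in the documents:** the number and normal distribution of the covariates, the retention threshold, the amount of missing data, and a linear model throughout (adherence status is to be logistic).

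**The case against.** The strongest reply is that these models exist to explore factors associated with outcomes. The trial's between-arm conclusions come from the unadjusted tests, selection is also to be guided by theory, and forced terms and thresholds are commonly left to an analysis plan. Much of this stands. The primary test is untouched, and theory may well lead the analysts to keep the arm. But nothing commits them to it, and the interactions are stated to assess whether the intervention effect differs across subgroups, which goes beyond describing prognostic factors. The general multiplicity sentence could cover the interaction tests if a procedure were named. It would not correct estimates and intervals taken after selection.

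Four stronger readings are tempting, and the documents do not support them:

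- *The trial could end with no intervention estimate at all.* Only an additional adjusted estimate is at risk. The Mann-Whitney, t and chi-square comparisons do not go through selection.
- *Elimination causes the 20–80% loss of the arm.* Those rates mostly restate low power for small effects, which the Limitations section already concedes. The harm is losing the interval and inflating what is kept.
- *Elimination causes the 23–28% of false modifiers.* A fixed model with the same number of interactions gives nearly as many.
- *Imputed results cannot be combined.* They can be if selection uses tests pooled across imputations, which gives one common model. The plan does not say this, but it does not rule it out.

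**Conclusion.** The point holds for the secondary adjusted and subgroup analyses, and only there. The plan states a selection rule that covers the intervention and its interactions and protects neither.

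The part that selection itself causes is the bias in what is reported. With 128 patients and removal at p<0.05, a true effect of 0.2 SD is reported on average as about 0.45 when it is reported, and 0.3 SD as about 0.47. At the design effect of 0.5 SD the exaggeration is modest (about 0.57). The chance of a false effect modifier, about 23–28% with five or six candidates, comes mainly from the number of interactions. It calls for naming fewer of them as well as for dropping the selection.

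The percentages rest on an assumed number of candidates, threshold and linear model. They show scale and are not predictions for this trial. The change should be made before analysis, but the primary conclusion does not depend on it.

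**What to change.** 1. Remove stepwise and backward elimination from any model used to estimate the intervention effect or its modification.
2. Keep the arm in every such model, with the T0 value where it is collected (I-CAT, USQNB-IC and the Autonomy Checklist have one; I-CAS and QUEST start at T1) and a short covariate list fixed in advance.
3. Name one or two interactions in advance, report each with its interval whatever its p-value, and label them exploratory. Two null interactions at 0.05 still give 1 − 0.95² = 9.75%, so the label matters.
4. If data-driven selection is wanted, confine it to a separate, hypothesis-generating prognostic model, with one common model across the imputed datasets.

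Fixed centre terms should not be required in the logistic model. Seventeen centres would add 16 parameters for 128 patients (128/17 = 7.5 per centre on average, with as few as 4 expected at some), which risks separation.

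The cost is a change of wording and fewer exploratory interactions examined. No extra patients or data are needed.
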